## Background

### Biological behavior

Desmoid-type fibromatoses are rare, non-metastasizing, locally aggressive soft tissue tumors. Aggressive fibromatoses can be located in every part of the body and are classified as extra-abdominal, abdominal wall or intra-abdominal [1, 2]. The abdominal wall is a predilection site in women of reproductive age [3]. Sporadic onset of the tumor is common, but an association with familiar adenomatous polyposis (FAP) has been documented, in particular in intra-abdominally localized aggressive fibromatoses [4]. The course of the disease is unpredictable and varies between relatively indolent, i.e. stabilization of the tumor, and progressive growth, which may halt spontaneously [5]. The reported frequency of recurrence following local treatment ranges from 5 to 63 % [6].

Genetic markers in tumor tissue have been analyzed, in particular the CTNNB1-gene. CTNNB1-gene encodes beta-catenin, a proto-oncogene involved in cell adhesion and cell transcription. Beta-catenin is a key factor in the Wnt-APC-beta-catenin pathway. On a cellular level the beta-catenin protein level is elevated in these tumors, implicating beta-catenin stabilization as a key factor in the pathogenesis of aggressive fibromatosis [7, 8]. Nuclear overexpression of beta-catenin is a histological condition used in a diagnostic. The diagnostic value is sensitive, but not specific [8–10]. Research on the CTNNB1-gene revealed 3 specific mutations, namely T41A, S45F and 45P [8, 10]. While it is yet unclear how these mutations precisely affect the aforementioned pathway in these tumors, a role in biologic behavior seems natural according to their role in pathogenesis. Several groups have analyzed CTNNB1-mutation and these mutations appear to have a prognostic value in determining the risk of recurrence in retrospective series of surgically treated patients [11–15]. Although Mullen et al. did not find a statistical significant prognostic [15], several other groups reported a higher risk of recurrence for patients with an S45F-mutation [11–13], even in multivariate analysis [12]. In addition, (surgical) trauma and hormones presumably play a role in the genesis of this tumor, as aggressive fibromatosis is known to arise in scars and in fertile females [16].

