### Study population

The study will take place in the Netherlands. All patients with extra-abdominal or abdominal wall aggressive fibromatosis are eligible for inclusion in the study. Primary and recurrent disease will be included, stratification will be done for analyses.

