### Sample size

Based on the incidence of sporadic aggressive fibromatosis and tumor localization, we expect to include 20 patients annually, we aim to include 100 patients in 5 years. Loss to follow-up or death is not to be expected. Under the most adverse conditions, a progression rate of 50 % would result in a 95 % confidence interval (95 % CI) of 40–60 %. A progression rate of 25 % would result in a 95 % CI of 18–34 %. We consider the presented 95 % CI to be acceptable for the study.

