### Statistical considerations

Statistical analysis will be carried out using IBM SPSS Statistics 21. Radiological measurements will be registered as a continuous variable at ratio. The average progression rate per year will be analyzed using data of all patients. The progression rate per year, defined as increase in size per tumor, using RECIST criteria, with the associated range and confidence interval, will be registered as the primary outcome. The QLQ-C30 questionnaire results in a score to classify the quality of life. This score will be registered as discrete data at ratio scale. If a score cannot be rewarded, the data of the questionnaire will be regarded as missing data. If a score is missing, but later registered scores are available, the later scores will be used in assessment of the quality of life. The overall quality of life will be calculated using data of all patients at the end of follow-up. The median value will be extracted with the associated range.

The possible influence of patient and tumor related factors on the progression rate and the quality of life are analyzed using the Kaplan-Meier method and univariable Cox-regression. Associations between variables will be explored by Chi-square analysis. Multivariate analysis will be performed if possible by means of Cox-regression. Those factors which prove to have statistical significance in univariate analyses, will be included in the multivariate analysis. The considerations for treatment will be categorized and analysis will show the occurrence of specific considerations.

The interim analysis of both primary and secondary parameters will be done after one year of follow-up on 20 patients. The analyses will be the same as described above and will be performed by the principal investigator. For all analyses, two-sided *P <* 0.050 is considered statistically significant.

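### The multivariable Cox model admits only factors with univariable P<0.05 and does not exempt CTNNB1, so the adjusted CTNNB1 effect may be lost or, when reported, inflated

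*Protocol article*

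**What the plan says.** All statements are in the protocol article.

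- **Univariable step (Statistical considerations).** The possible influence of patient and tumour factors on progression and quality of life "are analyzed using the Kaplan-Meier method and univariable Cox-regression".
- **Multivariable step (same section).** "Multivariate analysis will be performed if possible by means of Cox-regression". Entry is governed by one sentence: "Those factors which prove to have statistical significance in univariate analyses, will be included in the multivariate analysis". For all analyses, "two-sided *P <* 0.050 is considered statistically significant". No factor is exempt from the screen.
- **Aim (Abstract, Background; Secondary objectives).** Identifying factors associated with growth is an objective, and CTNNB1 mutation is the one factor given special mention. The Discussion says the study was designed to evaluate these factors under watchful waiting.
- **Sample size.** "we aim to include 100 patients in 5 years" and "Loss to follow-up or death is not to be expected". The size is justified only by the width of a CI for a progression proportion of 50% or 25%. No power is claimed for any prognostic factor.
- **Study population.** "Primary and recurrent disease will be included, stratification will be done for analyses".
- **Biological behavior.** "The abdominal wall is a predilection site in women of reproductive age", so site, sex and age are linked by the article's own account.

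**The concern.** Screening on univariable significance uses the same data first to choose the model and then to estimate it. This has three consequences.

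1. A real factor with modest power is often left out, and its adjusted effect is never estimated.
2. A factor that gets in does so because its estimate was large in this sample. The reported HR is then biased away from 1, and the P values and CIs of the final model do not have their nominal meaning.
3. A factor whose effect is masked by a correlated one can fail alone although it would matter jointly. Site, sex and age are candidates here.

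CTNNB1 is exposed to all three. The Discussion wants the result to help decide who can safely be watched and who would benefit from active treatment. An adjusted HR that is reported only when significant is a poor basis for that.

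**Working it through.** **Step 1: the plan's own figure.** The Wilson 95% CI with n = 100 gives 40.4–59.6% at 50% and 17.55–34.3% at 25%. Rounded, these are the stated 40–60% and 18–34%, so the sample-size figures reproduce. They concern a proportion and say nothing about factor analysis.

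**Step 2: inputs.**
- Patients: 100, without dropout (Sample size).
- Events: not stated. Reading the two planning rates as cumulative proportions gives 100 × 0.25 = 25 and 100 × 0.50 = 50. This is an assumption.
- Proportion p with the mutation of interest: not stated. Assumed 25%, varied from 10% to 25%.
- True HR: not stated. Assumed 2, varied up to 3. The article reports a higher recurrence risk for S45F after surgery but gives no size.
- Screen: two-sided 0.05.

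**Step 3: chance of passing the screen (Schoenfeld approximation).** SE(log HR) = 1/√(events × p × (1−p)), and power = Φ(log HR/SE − 1.96). For HR 2 (log HR 0.693) and p = 0.25:
- 25 events: SE = 1/√(25 × 0.1875) = 0.462; z = 1.50; power 0.32, so dropped in 68%.
- 50 events: SE = 1/√(50 × 0.1875) = 0.327; z = 2.12; power 0.56, so dropped in 44%.

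At p = 0.15 power is 0.24 and 0.42, so the factor is dropped in 76% and 58%. For 80% power at HR 2 and p = 0.25, 88 events are needed.

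**Step 4: check by simulation.** 3,000 univariable Cox fits were run per scenario, with 100 patients, exponential times and censoring at 60 months. At HR 2:

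| Mean events | p | Passes screen | Dropped | Median HR if selected |
|---|---|---|---|---|
| 25 | 10% | 29% | 71% | 3.5 |
| 25 | 20% | 37% | 63% | 2.9 |
| 25 | 25% | 40% | 60% | 2.9 |
| 50 | 10% | 43% | 57% | 2.8 |
| 50 | 20% | 58% | 42% | 2.4 |
| 50 | 25% | 63% | 37% | 2.3 |

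The approximation is somewhat pessimistic. At p = 0.25 the two methods together give dropping in 60–68% (25 events) and 37–44% (50 events).

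**Step 5: inflation.** Under the normal model, the mean log HR given z > 1.96 is log HR + SE × φ(c)/Φ(c), where c = log HR/SE − 1.96. For HR 2 and p = 0.25 the exponentiated values, which are geometric means, are 3.34 at 25 events and 2.51 at 50. The simulated medians are 2.9 and 2.3.

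**Step 6: where the problem is small.** With 50 events and p = 20% or 25%, the approximation gives 74% or 80% retained at HR 2.5 and 87% or 92% at HR 3. At HR 3 the simulated median selected HR is 3.1, so inflation has almost gone.

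**Step 7: false entries.** With five independent null factors, the chance that at least one passes is 1 − 0.95⁵ = 22.6%.

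**The case against.** **The size is assumed.** This stands. Events, prevalence and HR are all assumptions. Sample size gives a progression rate without a time unit, while the primary endpoint is a rate per year. If 25% were yearly, five years would give 1 − 0.75⁵ = 76%, or about 76 events, and power at HR 2 and p = 0.25 would be about 74%. The Discussion cites one series with about half of patients free of progression at 1 year, which allows more than 50 events. It also cites 6 of 27 and 16 of 70 progressing (22% and 23%), which fit the low end.

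**The loss is limited.** This also stands. Kaplan-Meier and univariable Cox results come first and are not filtered, so a dropped CTNNB1 still has a crude estimate. Only the adjusted one is lost. The multivariable step is conditional, the objective is secondary, and the primary endpoint is untouched.

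**A full prespecified model may be too large.** The article names three mutations. With wild type as reference they need three coefficients, and age, size and at least one for localization make six or more. That is a reason to fix the CTNNB1 coding, not to keep the screen.

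**A tempting stronger reading.** A reader might infer that the screen contradicts the stratification promised under Study population. The article does not support that. A Cox stratum, or separate analyses of primary and recurrent disease, need not pass a covariate screen, so both statements can be followed. Statistical considerations simply does not say how the stratification is done.

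**Conclusion.** The point holds as a badly chosen rule that the article itself states. It is not a detail left to an unseen document. As written, the adjusted effect of the study's named factor is reported only after a positive low-powered test.

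At a true HR of 2, a quarter of patients carrying the mutation and 25–50 events, the plan loses that estimate in roughly 37–68% of trials, depending on events and method, and exaggerates it when kept. With a larger effect (HR 2.5–3), 50 events and 20–25% prevalence, the factor usually enters, and at HR 3 the inflation is negligible. It would therefore be wrong to say that the rule will generally drop a real CTNNB1 effect. It performs worst with modest effects, rarer mutations and few events, and nothing in the article rules these out.

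**What to change.** Replace the screening sentence with a prespecified multivariable Cox model.

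- Keep CTNNB1 in the model whatever its univariable P value, as one prespecified contrast (for example S45F versus other) to save coefficients.
- Add a few factors the article already names (age, localization, baseline tumour size), also regardless of univariable P.
- Limit the coefficients to the events observed. At about 10 events per coefficient, an assumed rule of thumb, 25–50 events support about 2–5. If events are short, drop the lower-priority clinical factors first, in an order set beforehand, and never CTNNB1. A Firth-type fit is optional when events are few.
- Enter primary versus recurrent disease as a Cox stratum, which carries out the promise under Study population.
- Report all adjusted HRs with 95% CIs, and label any other factor exploratory.

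CTNNB1 is then always estimated, without a significance filter. The cost is a short rewrite, an early decision on CTNNB1 coding and factor priority, and less freedom to add factors later. A Firth-type fit may need software beyond SPSS 21.

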## Abstract

**Background:**

The efficacy of the classical treatment modalities surgery and radiotherapy in the treatment of aggressive fibromatosis is presently disputed and there is a shift towards a more conservative approach. The aim of the present study is to objectify tumor growth in patients with extra-abdominal or abdominal wall aggressive fibromatosis, while adhering to a “watchful waiting” policy. Other objectives are to investigate quality of life and to identify factors associated with tumor growth, in particular the relation with the presence of a CTNNB1-gene mutation in the tumor.

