**Design and methods:**

GRAFITI is a nationwide, multicenter, prospective registration trial. All patients with extra-abdominal or abdominal wall aggressive fibromatosis are eligible for inclusion in the study. Main exclusion criteria are: history of familiar adenomatous polyposis, severe pain, functional impairment, life/limb threating situations in case of progressive disease. Patients included in the study will be treated with a watchful waiting policy during a period of 5 years. Imaging studies with ultrasound and magnetic resonance imaging scan will be performed during follow-up to monitor possible growth: the first years every 3 months, the second year twice and the yearly. In addition patients will be asked to complete a quality of life questionnaire on specific follow-up moments. The primary endpoint is the rate of progression per year, defined by the Response Evaluation Criteria In Solid Tumors (RECIST). Secondary endpoints are quality of life and the rate of influence on tumor progression for several factors, such as CTNNB1-mutations, age and localization.

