## Discussion

During the last decade, there has been a shift in treatment strategy for aggressive fibromatosis from aggressive to conservative modalities. A watchful waiting policy is currently advised for extra-abdominal and abdominal wall aggressive fibromatosis [25]. Research validating the efficacy and applicability of a watchful waiting policy is limited. Mitchell et al. were the first to describe a stable phase for aggressive fibromatosis [5]. In a retrospective study of 17 patients under medical observation, all experienced at least one period of stable disease for over 6 months. A larger study by Fiore et al. evaluated 142 patients with primary and recurrent aggressive fibromatosis, treated with initial conservative treatment retrospectively [22]. Approximately 50 % of the patients did not have tumor progression after 1 year. Spontaneous regression has been reported by Salas et al. [18]. In a retrospective study analyzing 426 patients with aggressive fibromatosis, 27 patients were treated with a watchful waiting policy. Five of these patients had spontaneous remission, 16 patients stable disease and 6 patients had progressive disease. The median time to progression was 19.7 months. A recent study by [name] et al. reported 216 patients with primary extra-abdominal (*n =* 188) and intra-abdominal (*n =* 28) disease undergoing a diversity of treatments [24]. Initial wait-and-see policy was applied in 70 patients (60 extra-abdominal) and continued till the end of follow-up in 60 %. Progression occurred in 16 of the 70 patients, mostly treated with systemic modalities. These results demonstrate the potential safety of a watchful waiting policy.

Current knowledge on predictive factors is mostly based on surgical cohorts. Age, tumor localization and tumor size have been reported as predictive factors for the risk of recurrence following surgery. A nomogram was proposed by Crago et al. [27] using all these factors in a postoperative setting.

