In addition, CTNNB1-mutations are found to be a predictive factor for the risk of recurrence following surgery [12–14, 16]. The value of these factors in a postoperative setting cannot be extrapolated to a watchful waiting setting. The present study was designed to evaluate the role of these factors in relation to the progression rate in a watchful waiting setting. This information would help in determining which patients can safely undergo a watchful waiting policy, and which patients would benefit most from active treatment. The ability to predict tumor behavior would enable tailoring individual patient treatment and prevent over-or undertreatment.

The low incidence of aggressive fibromatosis presents a challenge for quality research. Collaborations between specialized institutions is essential. The prospective evaluation of predictive factors in a watchful waiting setting has been initiated by two other research groups. In France, Bonvalot et al. are conducting a similar study (ClinicalTrials.gov identifier NCT01801176). They have finished the inclusion process and are now conducting the final follow-up. In Italy, a similar study is coordinated by [name] et al. (ClinicalTrials.gov identifier NCT02547831). This study is still open and we encourage inclusion. The present study was designed to resemble the French and Italian study, to facilitate a possible merging of the data if the inclusion rate in the studies would be disappointing. Main inclusion and exclusion criteria match for all three studies, though our study also includes patients presenting with recurrent disease.

The occurrence of aggressive fibromatosis has been related to hormonal influences and pregnancy by Häyry and Reitamo et al. [16, 28]. Although hormonal levels and receptors on the tumor have not been investigated, the occurrence of disease among fertile females is very suggestive. A recent study by van Broekhoven et al. evaluated time trends in the Dutch population [29]. Their analysis between incidence and hormonal influences did not show a positive correlation. In an attempt to evaluate the hormonal influence, data on the use of hormonal medication and history of pregnancy will be collected during the present study.

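### Every prognostic factor is tested against progression and quality of life at P < 0.050 with no key test or exploratory label, leaving a substantial chance of a false predictor

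*Protocol article*

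**What the plan says.** Statistical considerations closes with a blanket rule: "For all analyses, two-sided *P <* 0.050 is considered statistically significant". Earlier in that section the factor analyses are given two outcomes: "The possible influence of patient and tumor related factors on the progression rate and the quality of life are analyzed" by Kaplan-Meier and univariable Cox regression. Entry to the multivariable model depends on the same threshold: "Those factors which prove to have statistical significance in univariate analyses, will be included in the multivariate analysis". The only analyses there described in exploratory terms are the Chi-square associations between variables.

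The factors are named in several places:
- The abstract (Design and methods) lists as a secondary endpoint "the rate of influence on tumor progression for several factors, such as CTNNB1-mutations, age and localization". The words *such as* leave the list open.
- The Discussion adds tumor size: "Age, tumor localization and tumor size have been reported as predictive factors for the risk of recurrence following surgery". It then adds CTNNB1 and says of these factors: "The present study was designed to evaluate the role of these factors in relation to the progression rate in a watchful waiting setting".
- The Discussion also says that hormonal medication and pregnancy history will be recorded, to look at hormonal influence.

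One factor is given emphasis. The abstract (Background) speaks of factors associated with growth, "in particular the relation with the presence of a CTNNB1-gene mutation in the tumor". On the use of the results, the Discussion says: "This information would help in determining which patients can safely undergo a watchful waiting policy, and which patients would benefit most from active treatment".

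**The concern.** The article names a factor of main interest, but its analysis gives that factor no separate status. A CTNNB1 result at P = 0.03 would carry the same label as a result at P = 0.03 for any other factor, on either outcome. With several factors and two outcomes each tested at the full 0.05, the chance that at least one comes out significant by luck is well above 5%.

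What is at stake is how a chance result is read. If it is reported as a significant predictor, it could influence who is offered watchful waiting and who is steered to active treatment, which is the use the Discussion has in mind. The rule is also stated, not left open: a later analysis plan that introduced a hierarchy would have to depart from the published sentence covering all analyses.

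**Working it through.** **The plan's own figures.** The only design figures are the confidence intervals under Sample size. With n = 100 and z = 1.96, the Wilson interval is [p + z²/2n ± z√(p(1−p)/n + z²/4n²)] / (1 + z²/n).
- p = 0.50 gives 40.4–59.6%; the article states 40–60%.
- p = 0.25 gives 17.5–34.3%; the article states 18–34%.

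Both reproduce. They concern estimation of a progression proportion. The article states no power and no error rate for the factor tests.

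**Inputs.**
- Level: 0.05, two-sided, for all analyses (Statistical considerations).
- Outcomes: two, progression and quality of life (Statistical considerations).
- Factors expressly tied to progression: four, namely CTNNB1, age, localization and tumor size (abstract, Discussion).
- Further factors collected for evaluation: two, hormonal medication and pregnancy history (Discussion).
- Assumptions: no factor matters, and there is one test per factor and outcome. The correlation between test statistics is not given in the article, so a range of 0 to 0.8 is shown.

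**Independent tests.** The chance of at least one P < 0.05 among k null tests is 1 − 0.95^k.
- k = 4: 1 − 0.8145 = 18.5%.
- k = 6: 1 − 0.7351 = 26.5%.
- k = 12 (six factors on two outcomes): 1 − 0.5404 = 46.0%.

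**Correlated tests.** For normal test statistics with common correlation ρ, the chance is 1 − E[{Φ((1.96 − √ρ·U)/√(1−ρ)) − Φ((−1.96 − √ρ·U)/√(1−ρ))}^k], with U standard normal. Numerical integration gives:

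| Tests | ρ = 0 | ρ = 0.5 | ρ = 0.8 |
|---|---|---|---|
| 4 factors, progression | 18.5% | 15.6% | 11.4% |
| 6 factors, progression | 26.5% | 20.7% | 13.9% |
| 6 factors, both outcomes | 46.0% | 31.9% | 18.6% |

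**Does the multivariable step protect?** Hardly. A simulation of the univariable-then-multivariable filter (linear-model approximation, 100 patients, seven independent null factors, 4,000 runs) left at least one significant factor in 30.6% of runs. Without the filter, 1 − 0.95^7 = 30.2%. Seven is used here only to illustrate the filter.

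**What would a correction cost?** Schoenfeld's formula gives power = Φ(√(d·q(1−q))·ln HR − z). Assume d = 50 events, HR = 2 and a factor split 50:50 (q = 0.5). None of these is in the article as a design value. Then √12.5 × 0.693 = 2.451.
- At 0.05: Φ(2.451 − 1.960) = 69%.
- At Bonferroni 0.05/6 = 0.0083: Φ(2.451 − 2.638) = 43%.

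**The case against.** The strongest reply is that this is ordinary practice in a suitable setting. GRAFITI is an observational cohort in a rare disease. Its primary outcome is estimated with a confidence interval, its sample size rests on interval width, and the factor work is listed among secondary or other objectives. Univariable screening at 0.05 is conventional there, and multiplicity is often left to an analysis plan. A correction would be costly, as the fall from 69% to 43% shows. Much of this stands. It limits the seriousness of the point and argues against requiring a correction. It does not remove the point, because secondary rank does not make a result exploratory when the text calls it statistically significant at 0.05.

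Several stronger readings are tempting, and the article does not support them:
- *At least seven factors are tested.* That count needs primary versus recurrent disease, which Study population names only as a stratification. Six can be traced, and only four are expressly tied to progression.
- *A false predictor is likely.* Even odds are not reached with six factors on both outcomes and independent tests (46.0%). Half of those tests concern quality of life, where a chance hit is not a false predictor of progression.
- *Significant factors are presented as proven.* The sentence "Those factors which prove to have statistical significance in univariate analyses, will be included in the multivariate analysis" is a model-entry rule; its verb means *turn out to have*.
- *CTNNB1 is the only factor with prior support.* The Discussion cites evidence from surgical cohorts for age, localization and size as well.
- *The results will decide treatment.* The Discussion says only that they would help in determining patient selection.

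**Conclusion.** The point holds in a limited form. The article fixes two-sided 0.05 for every factor test on both outcomes and gives no test key status, even though it names CTNNB1 as the main factor of interest. If no factor matters, the chance of at least one significant factor for progression is 11.4–18.5% for the four factors expressly tied to it and 13.9–26.5% for six. Six factors on both outcomes give 18.6–46.0%. In each range the lower end is correlation 0.8 and the upper end is independence.

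These figures assume that every null hypothesis is true and that each factor is tested once per outcome. Real effects among the factors would leave fewer null tests and a smaller chance of a false one. Adding factors from the open list, splitting CTNNB1 by the three mutations named in the Background, or counting the interim look at 20 patients, which repeats the same analyses, would raise the chance. The primary endpoint is not affected. The issue is how secondary findings are labelled and used, and it is worth correcting because the correction is cheap.

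**What to change.** In Statistical considerations, replace the blanket threshold with two statements:
1. CTNNB1 mutation status versus time to progression is the single key factor test, at two-sided 0.05. The comparison should be defined so that it is one test.
2. All other factor analyses, including every factor analysis of quality of life, are exploratory. They are reported as hazard ratios or other estimates with 95% confidence intervals, without claims of statistical significance.

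Add to the Discussion that exploratory factors need confirmation before they guide patient selection, for example in the French and Italian cohorts that the article describes as similar in design.

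This keeps the error of the one key claim at 5%. Holm or Bonferroni across all factors is not required and, given the power loss shown, would be a debatable trade.

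The cost is wording only, with no extra patients or data. Under Methods, CTNNB1 analysis is to be done after all patients are included unless status is already known, so the key test can be fixed before most of those results exist. The downside is that age, localization, size and the hormonal factors could not be claimed as established predictors from this study alone, although some of them also have prior evidence from surgical cohorts.
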